## Abstract

**Background:**

Anxiety, Depression and Somatoform (ADSom) disorders are highly prevalent in primary care. Managing these disorders is time-consuming and requires strong commitment on behalf of the General Practitioners (GPs). Furthermore, the management of these patients is restricted by the high patient turnover rates in primary care practices, especially in the German health care system.

In order to address this problem, we implement a complex, low-threshold intervention by an Advanced Practice Nurse (APN) using a mixture of case management and counseling techniques to promote self-management in these patients. Here we present the protocol of the “**S**elf-**M**anagement Support for **A**nxiety, **D**epression and **S**omatoform Disorders in Primary Care” (**SMADS**)-Study.

**Methods/Design:**

The study is designed as a cluster-randomized controlled trial, comparing an intervention and a control group of 10 primary care practices in each case. We will compare the effectiveness of the intervention applied by an APN with usual GP-care. A total of 340 participants will be enrolled in the study, 170 in either arm. We use the Patient Health Questionnaire-German version (PHQ-D) as a screening tool for psychiatric symptoms, including patients with a score above 5 on any of the three symptom scales. The primary outcome is self-efficacy, measured by the General Self-Efficacy Scale (GSE), here used as a proxy for self-management. As secondary outcomes we include the PHQ-D symptom load and questionnaires regarding coping with illness and health related quality of life. Outcome assessments will be applied 8 weeks and 12 months after the baseline assessment.

**Discussion:**

The SMADS-study evaluates a complex, low threshold intervention for ambulatory patients presenting ADSom-symptoms, empowering them to better manage their condition, as well as improving their motivation to engage in self-help and health-seeking behaviour. The benefit of the intervention will be substantiated, when patients can enhance their expected self-efficacy, reduce their symptom load and engage in more self-help activities to deal with their everyday lives. After successfully evaluating this psychosocial intervention, a new health care model for the management of symptoms of anxiety, depression and somatoform disorders for ambulatory patients could emerge, supplementing the work of the GP.

**Trial registration:**

Clinicaltrials.gov Identifier: NCT01726387

## Background

Anxiety disorders, depression and somatoform disorders (hereafter referred to as ADSom disorders) belong to the most common mental disorders in primary care [1]. ADSom disorders contribute to a substantial utilization of the health care system [2]. Also, ADSom disorders cause significant direct and indirect health care costs [3].

### Mental disorders – an urgent problem in primary health care

There is no controversy about the pivotal role of primary care in treating these mental conditions: most patients with ADSom symptoms are primarily and often exclusively seen by their general practitioner (GP) [4-6]. A survey conducted by the Bertelsmann Foundation [7] revealed only 13% of patients with psychological complaints over the past 12 months were seeking solely specialized care. Moreover, ADSom-disorders are frequently associated with, or sometimes masked by, somatic disorders, therefore, an additional somatic medical examination by the GP is necessary [8]. Not least, the World Health Organization recommends the integration of mental health care into primary care. It “enhances access, promotes respect of human rights, is affordable and cost effective, and generates good health outcomes” [9].

However, targeting the many problems these patients convey exceeds the resources of most GPs. Also, high patient turnover rates in primary care inevitably limit contact time between GP and patients: In Germany, an average of 18 primary-care-contacts per year per patient in 2007 [10], even 35–54 contacts per year for multi-morbid patients [11], render it impossible to discover and unveil backgrounds and/or motifs of the psychological symptoms and complaints. Regular consultations focus mainly on acute care, thus falling too short to enhance and support self-management skills of the patients. Professional self-management support is beyond the scope of usual GP-care, although self-management support through patient education and counseling is a cornerstone of mental health care [12].

The German social security system offers quite a few different services for patients in psychosocial need: helpdesks, helplines, publicly-funded self-help groups, counseling services, community based social-psychiatric support, rehabilitation services, re-integration services after long sickness leaves, and if nothing else: psychotherapy. Even though the services are there, more often than not ADSom-patients are not able to help themselves by taking the next step - accessing a service. There is paperwork to do, contacting, networking, information seeking and so on – tasks patients with psychological complaints have a hard time executing. Symptoms prevent the utilization of available services [13]. Finally, there is a lack of coordination amongst these services as they are offered in an unsystematic and erratic way. Depending on the information they have, GPs recommend certain services to their patients, but quite a few are reluctant to get involved in the time-consuming, usually not reimbursed methods of accessing these services. In order to supplement patient management, we introduce a specially trained Advanced Practice Nurse (APN) working alongside a GP in the practice.

Several trials support this collaborative care model. Health care assistants helped to reduce patients’ depressive symptoms in the PROMPT-Study [14]. Elderly patients showed long-term improvement in their depressive symptomatology in the IMPACT-trial [15]. A program to manage depression interprofessionally proved to be effective in the INDI-trial [16].

A recent Cochrane review concludes: “Collaborative care is associated with significant improvement in depression and anxiety outcomes compared with usual care, and represents a useful addition to clinical pathways for adult patients with depression and anxiety” [17].

In recent years, Germany has begun to gradually change its legislation to allow health care professionals like APNs to deliver services for patients. The law now facilitates the delegation of a wide variety of health services from a GP to a health care assistant or an APN. In spring 2012 a directive for the delegation of medicinal work to other health care professions (“Heilkundeübertragungsrichtlinie”) was put into action by the Joint Federal Commission, a ruling body for health care services in Germany [18].

Based on that directive we implement a complex, low-threshold intervention by an APN using case management and counseling techniques to support ADSom-patients. The APNs will help the patients to better understand their symptoms and complaints, identify stressors and resources, as well as create goals to be attained in the course of the intervention.

Here we report the study protocol of the “**S**elf-**M**anagement Support for **A**nxiety, **D**epression and **S**omatoform Disorders in Primary Care” (**SMADS**)-Study.

### Objective

The objective of the study is to examine the effects of counseling and case management on the concept of self-efficacy. We want to investigate whether an APN, collaborating with a GP, addressing the psychosocial needs of ADSom-patients can enhance the patients self-efficacy (a proxy for self-management) compared to usual care.

Furthermore, we want to know if an APN decreases patients’ symptom loads and psychosocial burdens, and increases their quality of life, while reducing health care utilization. A further assignment of the APN is to implement case management elements into the primary care practice. After all, we want to estimate whether cooperation between an APN and a GP does improve health care services for these patients.

The study is part of “Psychenet - Hamburg Network for Mental Health” (http://www.psychenet.de/en.html) - a network in the Hamburg region consisting of more than 60 scientific and medical institutions, counseling centers, governmental authorities, private companies, health insurances as well as patients’ and relatives’ associations. Its purpose is to work on testing innovative care models which aim to make decisive improvements to the prevention, diagnosis and treatment of people with mental illnesses in the region [19].

## Methods

### Study design

We set up an open label, cluster-randomized controlled trial. We randomly allocate participating general practices to either the interventional arm, in which a nurse-led collaborative care model is implemented, or to the control arm in which the GP continues his/her usual routine care treating ADSom-patients.

The APN will work directly in the primary care practices. All participants will be assessed at baseline, 8 weeks post-baseline and 12 months post-baseline. The scheduled time for providing services in the interventional primary care practices is 12 months. In the control practices, the patients obtain the „usual care“ by the GP. In this arm, the course of the disease and the utilization of GPs or other professions will be documented. The interventions will take place in the general practices, the APNs having an own office at their disposal. The practice and the APN arrange a fixed weekday on which the nurses work in this particular practice. Figure 1 illustrates patient flow of the SMADS-study.

**Figure 1 F1:**
[figure not shown]
CONSORT flowchart for recruitment of practices and patients (projected).

### Ethics approval

Ethics approval was obtained from the Ethics Committee of the Hamburg Medical Association in October 2012, approval number PV4106.

### Recruitment of the primary care practices

The city of Hamburg is a large metropolitan area with a population of 1,8 million. There are about 1000 primary care practices, about 70% of which are owned and operated by a single GP and his/her practice assistants, while about 30% are group practices.

The recruitment of the 20 GP-practices (10 in the interventional arm, 10 in the control arm of the study) will occur through a letter of invitation mailed out to 500 primary care practices in five districts of Hamburg city, according to the zip code. If they show interest, the trial will be introduced in more detail. Practices which don’t respond at all will be selectively recalled to ask for the reasons (see Figure 2).

**Figure 2 F2:**
[figure not shown]
Planned recruitment of primary care practices.

### Modules of the complex, psychosocial intervention

Promoting self-management is the target of the planned complex intervention. Strategies of self-management support are based on knowledge and information transfer to increase health literacy and facilitate the development of skills, as well as promoting the use of available health resources [12]. Self-management support promotes control and responsibility, thus strengthening the patients’ confidence in their own ability to manage his or her psychological symptoms, as well as their impact on his or her daily life [20].

More explicitly, the aim of any self-management in psychological complaints is to empower the patient:

• to actively pursue the challenges in dealing with mental symptoms and syndromes,

• to develop an adequate strategy for dealing with the negative side effects,

• to set up an appropriate symptom management,

• to use problem solving skills in order to manage daily life, and

• to support the patients and their families on their way to become qualified (lay)-experts in their own right, as well as

• to prevent chronification, thus to contribute to the prevention of personal dependency and home care [21].

The intervention is comprised of several modules to engage the patient in better self-management and self-care (Figure 3):

1) Support in finding psychotherapeutic treatment: Following the indications for psychotherapeutic treatment, having the APN explain different options, support in contacting a therapist,

2) Information about disease: Supporting / extending explanations of the GP, plus four behaviour-modifying modules at the disposal of the APN which directly target the self-management activities of patients such as:

3) Developing daily activities schedules,

4) Coping with daily hassles,

5) Using problem-solving skills,

6) (Re)-engaging in his / her social network, and community activities, as well as

7) Learning relaxation techniques to enable the patients to reduce their stress levels on their own and

8) Supporting the patient in making contact with community based psychosocial services and self-help groups.

### Advanced practice nurse

We decided to employ nurses experienced in the management of patients with psychiatric symptomatology or psychosocial needs, preferably having either a background in primary care or a bachelor of science in nursing. Closely monitored by the study-GP, the APNs go through a training program incorporating written documentation and practical training, live enactments with simulated patients, and sitting in on therapy in psychiatric wards or a psychosomatic outpatient clinic.

Since we have created the job profile with part-time potential, an APN will need to be quite mobile and flexible. They are supposed to rotate between up to five different practices, handling a different working environment and different working hours every weekday.

### Study population and recruitment

The study is conducted in the city of Hamburg. Citywide, half of the GPs are asked to participate. Additionally, we will recruit GPs by introducing the project in quality circles and contacting the Hamburg Association of General Practitioners. As we build up the APN staff step by step we include practices in a similar mode. The process of recruiting practices is ongoing.

Inclusion criteria for practices are:

• Willingness to participate in the study regardless of randomization to the intervention or control arm,

• One single private room at scheduled times for the APN to deliver the intervention in a protected environment,

• No psychotherapeutic treatment within the practice, neither by the GP him/herself nor by any other professional in the practice,

• No participation in other studies of “Psychenet: Hamburg Network for Mental Health”.

The patient recruitment is based on an assessment taking place in the practice on a particular screening day. As the capacity of the APN is limited, and we don’t want to create waiting lists, it is required to recruit patients into the study adjusted to the APN’s treating capacity.

The first part of the assessment is done by the GP: All patients who are seen by the doctor on the screening day, will be put on a chart and checked for inclusion criteria.

Eligibility criteria for patients are:

1) PHQ ≥ 5 on the anxiety, depression or somatoform scale,

2) Age: 18–65 years old,

3) Literacy (German),

4) Fully able to give consent,

5) Sufficient auditory and visual capabilities,

6) Currently no psychotherapeutic treatment.

### PHQ-D-assessment

Patients found eligible will be informed about the study. The patient will receive written and verbal information from the GP. The information covers the aims and procedures of the study, the selection of participants, the data collection, processing and storage, as well as possibilities for cancellation. In case these terms are accepted, the participants will have to sign an informed consent form to participate in the study. Besides that, patients have to agree to release their physician of his/her medical confidentiality allowing the APN and the GP to exchange information. Patients will be asked to complete the “Patient Health Questionnaire-D (PHQ-D)” [24] and other instruments introduced later in this paper.

The target population for the intervention are adults aged 18 to 65 scoring ≥5 on any of the three symptom scales that are incorporated in the PHQ-D: Anxiety, using the seven items of the General Anxiety Disorder-Scale (GAD-7); Depression, using the nine items of the PHQ-9 depression scale; or somatoform symptoms which are checked by the fifteen-item somatization scale of the PHQ, PHQ-15.

Psychiatric symptoms fluctuate on a daily basis and overlap between the disorders [8]. Thus, we expect many patients to score above the cut-off on any of the scales. A score as low as ≥5 to gain access to the counseling service in the GP practice emphasizes the low-threshold approach of the intervention. When considering prevention, early support may impede a chronic condition later on.

### Exclusion criteria

We limit the exclusion to the negation of the inclusion criteria. Also, participation in other studies of our department will exclude a patient from this study. Moreover, we didn’t enroll terminally ill or immobile patients, or patients who are not regulars in the practice.

### Sample size/power calculation

We calculated a sample size of 220 patients based on an expected difference between the intervention and the control group of 2.7 points and a common standard deviation of 5.4 points on the General Self-efficacy scale as the primary outcome 12 months post baseline. assuming an intra-cluster correlation of 0.05, we will attain a sufficient study power of 80%. For that we need a minimum of 20 randomized clusters, with an average cluster size of 11 patients. Assuming a drop-out rate of 33% on the patient level, we have to recruit 340 patients (on average 17 patients per cluster). The planned numbers and the patient flow are shown in Figure 4.

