### Statistical analyses

For the primary outcome we evaluate the changes in comparison to the baseline GSE after 12 months. A linear mixed model will be calculated for the difference between the intervention and control groups. The variable “group” will be considered a fixed effect while the practice will be considered a random effect under the control of the baseline covariates (baseline values of GSE and other confounders like PHQ-D, age, gender, education, utilization of the health care system on patient level, as well as age, gender, status of practice (single or group) on practice level. The two-sided α-level was set to 0.05.

The analyses of the primary outcome will be based on an intention-to-treat-(ITT)-analysis: All patients enrolled into the study will be analyzed at follow-up. All drop-outs not having withdrawn their consent will be asked again to take part in the final assessment 12-months-post-baseline. If patients reject this invitation or cannot be reached at all, their values will be imputed using the last-observation carried forward (LOCF) method.

The robustness of the results will be investigated performing sensitivity analyses with different methods of imputing missing values.

The same procedures will be applied for the PHQ-D, the EQ-5D and the „Coping with Illness scale“ as secondary outcomes. There will also be analyses of the observed cases (OC). These analyses will include only those patients, who did not drop out and completed the final assessment.

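### The stated 80% power and 2.7-point target fit about 220 patients observed at 12 months, but the primary analysis is all enrolled patients with LOCF, which can dilute the estimate to about 1.8 points

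*Protocol article*

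**What the plan says.** The section on sample size and power starts from an "expected difference between the intervention and the control group of 2.7 points". The variability assumed at 12 months is "a common standard deviation of 5.4 points on the General Self-efficacy scale". It arrives at 220 patients in 20 practices averaging 11 each and concludes: "assuming an intra-cluster correlation of 0.05, we will attain a sufficient study power of 80" per cent. It then inflates for loss: "Assuming a drop-out rate of 33% on the patient level, we have to recruit 340 patients (on average 17 patients per cluster").

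The section on statistical analyses describes something else for the primary outcome. Under intention to treat, "All patients enrolled into the study will be analyzed at follow-up". Drop-outs who have not withdrawn consent are approached again for the 12-month assessment. If they refuse or cannot be reached, "their values will be imputed using the last-observation carried forward (LOCF) method". The study design section schedules assessments at baseline, 8 weeks and 12 months, so the carried score is a baseline or a week-8 score. Sensitivity analyses with other imputation methods and an analysis of observed cases are planned in addition. The hypotheses section sets the expected improvement at about 2.7 points.

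**The concern.** Dividing by the retention rate makes sense when drop-outs are absent from the analysed set: 340 are recruited so that about 220 have a 12-month value. In the primary analysis, however, the drop-outs are present. That changes two things that the calculation holds fixed. The analysed cluster rises from 11 to 17 patients, and with it the design effect. Up to a third of the outcome values may also be early scores: a baseline score holds no treatment effect, and a week-8 score comes early in a service scheduled to run for 12 months. Extra recruitment protects the number of completers but not the size of the difference once LOCF is applied.

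Two things are at stake. The quoted 80% is not shown to be a property of the primary analysis. And a primary estimate read against 2.7 points may fall short only because early scores stand in for 12-month scores, and be taken as lack of effect.

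**Working it through.** **Inputs.** From the sample size section: difference 2.7, SD 5.4, ICC 0.05 ("assuming an intra-cluster correlation of 0.05"), 20 practices, 11 patients per practice in the calculation and 17 recruited, drop-out 33%. From the statistical analyses section: "The two-sided α-level was set to 0.05". The article prints no formula. I use design effect DE = 1 + (m − 1) × ICC, SE = √(4 × SD² × DE / N), and a two-sided t test on 20 − 2 = 18 df.

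**1. The plan's own figure.** With m = 11, DE = 1 + 10 × 0.05 = 1.5. SE = √(4 × 5.4² × 1.5 / 220) = 0.892. The ratio 2.7 / 0.892 = 3.03 gives power 81.7% (85.7% by normal approximation). The stated 80% is reproduced. Recruitment: 11 / 0.67 = 16.4, rounded up to 17, and 17 × 20 = 340. That also holds.

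**2. The primary analysis set.** With N = 340 and m = 17, DE = 1 + 16 × 0.05 = 1.8. SE = √(4 × 5.4² × 1.8 / 340) = 0.786.

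**3. Dilution.** Let p be the share imputed and r the fraction of the 12-month effect already present in carried values. The expected difference is 2.7 × [1 − p(1 − r)]. Unadjusted power (t, 18 df):

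| p | r | Expected difference | Power |
|---|---|---|---|
| 33% | 0 | 1.81 | 58.6% |
| 33% | 25% | 2.03 | 68.6% |
| 33% | 50% | 2.25 | 77.4% |
| 33% | 75% | 2.48 | 84.6% |
| 33% | 100% | 2.70 | 90.1% |
| 20% | 0 | 2.16 | 73.9% |
| 10% | 0 | 2.43 | 83.2% |

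An expected difference of about 2.33 is needed for 80%. At p = 33% that means r = (2.33 / 2.7 − 0.67) / 0.33, or about 58–59%. The normal approximation gives 63.4% at r = 0 and break-even near 45%. If 120 of 340 are imputed (35%), the zero-effect case is 55.7%, so 59% is not a strict floor.

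**4. With the planned baseline adjustment.** A patient whose baseline is carried forward has a change of exactly zero, so noise shrinks together with effect. Scaling the SD by √(1 − ρ²) misses this, so simulation is needed. Settings: 33% imputed, all from baseline, no effect carried, practice-level ANCOVA, 2,500 runs. ρ is the baseline to 12-month correlation. All correlations are assumptions, because the article gives none. Each pair is power without / with three practice-level covariates that have no effect of their own:

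| ρ | Practice-level correlation | LOCF, all enrolled | Completers, same model |
|---|---|---|---|
| 0.3 | 0 | 78 / 67% | 82 / 74% |
| 0.3 | 0.5 | 83 / 74% | 87 / 79% |
| 0.5 | 0 | 81 / 74% | 84 / 76% |
| 0.5 | 0.5 | 89 / 81% | 92 / 84% |
| 0.7 | 0.5 | 94 / 88% | 96 / 91% |

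REML mixed-model fits of the LOCF analysis (1,000–1,500 runs per setting) agree within 2 points and give a mean estimate of about 1.8. Against completers under the same model, LOCF costs 2 to 7 points of power in these settings.

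**The case against.** The strongest reply is that nothing is miscalculated. Sizing a trial on evaluable patients and inflating for loss is ordinary practice, and both 80% and 340 can be reproduced. That stands: this is a mismatch between two sections, not an arithmetic error.

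A reader might go further and infer that the protocol's own inputs show a trial with only 59% power. The documents do not support that. No formula is given, and 59% needs three additions: all 33% are imputed, none of them carries any effect, and baseline GSE is ignored. The text points away from each. Drop-outs who keep their consent are contacted again, and they include patients who merely abandoned the intervention, so the imputed share may be below 33%. Week-8 scores may be the ones carried forward. The planned model adjusts for baseline GSE. With 2.7 points in all 340 patients, unadjusted power is about 90%.

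The lower figures with practice-level covariates do not count against LOCF in particular. Spending degrees of freedom on 20 practices also lowers the completer analysis, which falls below 80% in three of the five settings.

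It is also fair to say that the planned sensitivity and observed-case analyses would reveal dilution. They limit the harm but do not remove it, because the primary result is still the LOCF one. What remains is that the article gives both a power and a primary handling of missing values, that the two do not belong together, and that it states no assumption about the effect in carried values to connect them.

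**Conclusion.** The concern holds as an inconsistency between the sample size section and the primary analysis. The 80% and the 2.7-point target belong to about 220 patients observed at 12 months. For the planned ITT analysis with LOCF, the article establishes neither.

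The firm consequence is dilution: up to one third of the target (2.7 to about 1.8) if 33% are imputed and all from baseline, less if drop-outs are recovered or week-8 scores already show part of the effect. The consequence for power is uncertain and probably modest. The unadjusted range of 59% to 90% reflects an unknown carried effect. With baseline GSE adjustment, the worst case is about 78–94% under the assumed correlations, a few points below completers. The documents do not show that the trial is materially underpowered.

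**What to change.** Preferred: make the primary analysis a likelihood-based mixed model on the observed 8-week and 12-month GSE values of all enrolled patients, with practice as random effect and the planned baseline adjustment, and take the 12-month difference from it. State the missing-at-random assumption. The 220-observed calculation and the 2.7-point target then apply to the primary analysis. Keep LOCF as one of the sensitivity analyses already foreseen.

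If LOCF stays primary, restate the power in the sample size section for 340 patients, 17 per practice and design effect 1.8, with the assumed share imputed and the assumed fraction of the effect in carried values. Say in the hypotheses section that the LOCF estimate may be smaller than 2.7.

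Either change costs a few sentences. The second may produce a less favourable stated power. Neither needs more patients.
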